### Criteria for discontinuing or modifying allocated interventions {11b}

There have not been observed serious complications for PLCD [27]. Furthermore, there have been reported some short-term and long-term complications for the ketogenic diet. Short-term complications are dehydration, hypoglycemia, lethargy, and gestational side effects (diarrhea, nausea, and vomiting), while long-term complications are hypercalcemia, lipid profile change, urolithiasis, gallstone, and hair loss [28]. As the trial studies have been done for a short time ((12 weeks) [21], (6 weeks) [22]) and reported the beneficial effects of the ketogenic diet without any adverse complications, our trial will be conducted for short time (8 weeks) as well. The dietitian will also announce each participant of the complications of their diet and remind them to stop their diet if they feel any adverse effects or discovered they are pregnant.

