### Adverse event reporting and harms {22}

As previously mentioned, these two diets do not have serious adverse or harmful effects on short time. It seems that the ketogenic diet demonstrates some adverse events (AEs) such as dehydration, hypoglycemia, lethargy, and gestational side effects (diarrhea, nausea, and vomiting) for a short time and serious adverse effects (SAEs) like hypercalcemia, lipid profile change, urolithiasis, gallstone, and hair loss for long-term intervention. Since our trial will be conducted for a short time (8 weeks), it is predicted to have no SAEs. However, each participant will be informed of the side effects of their diet by a dietitian and will be reminded to stop the diet if they experience any AEs or discover they are pregnant. Moreover, SAEs will be reported to the DMEC, indicating expectedness, seriousness, severity, and causality.

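### The harms section labels ketogenic-diet complications AE or SAE by time of onset, not by seriousness, and only the SAE label has a stated route to the DMEC

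*Protocol article*

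**What the plan says.** Criteria for discontinuing or modifying allocated interventions {11b} divides the known complications of the ketogenic diet (KD) by time. The early group is given as "Short-term complications are dehydration, hypoglycemia, lethargy, and gestational side effects (diarrhea, nausea, and vomiting". The late group follows in the same sentence, worded as "while long-term complications are hypercalcemia, lipid profile change, urolithiasis, gallstone, and hair loss". For the portfolio low-carbohydrate diet (PLCD) it says: "There have not been observed serious complications for PLCD". It also describes two cited ketogenic-diet trials, of 12 and 6 weeks, as free of adverse complications.

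Adverse event reporting and harms {22} goes over the same ground with different labels. The early effects are now "some adverse events (AEs) such as dehydration, hypoglycemia, lethargy, and gestational side effects (diarrhea, nausea, and vomiting) for a short time". The late effects, by contrast, have turned into "serious adverse effects (SAEs) like hypercalcemia, lipid profile change, urolithiasis, gallstone, and hair loss for long-term intervention". It continues: "Since our trial will be conducted for a short time (8 weeks), it is predicted to have no SAEs". Each participant "will be reminded to stop the diet if they experience any AEs or discover they are pregnant". The reporting rule is: "SAEs will be reported to the DMEC, indicating expectedness, seriousness, severity, and causality".

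Provisions for post-trial care {30} gives as its reason for making no provision that neither diet has shown adverse effects.

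**The concern.** AE and SAE are regulatory categories. What makes an event serious is its consequence for the patient, not how long she has been on the diet. Hypoglycemia or dehydration in week 3 can put a woman in hospital; hair loss or a shift in cholesterol after long use usually need not be serious at all. Section {22} attaches the labels the other way round.

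This matters because the labels stand directly before a rule that uses them. SAEs go to the DMEC; for AEs the section says only that participants are told of side effects and reminded to stop the diet. If site staff take the lists as a guide, the harms most likely to appear within 8 weeks are the ones listed outside the committee's stated route. The section lists harms for the KD arm only, so the effect falls mainly on that arm. The same literal reading would make a change in lipids, measured before and after treatment in all women, a serious event.

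**Working it through.** No figure in the plan is to be reproduced here. The check is a comparison of the two lists, followed by the inference drawn from them.

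**Step 1: match the lists.**

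| KD complications | Label in {11b} | Label in {22} | Items matching |
|---|---|---|---|
| dehydration, hypoglycemia, lethargy, diarrhea, nausea, vomiting | short-term | AE | 6 of 6 |
| hypercalcemia, lipid profile change, urolithiasis, gallstone, hair loss | long-term | SAE | 5 of 5 |

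Total: 6 + 5 = 11 items, all carried over, none moved between the lists. If diarrhea, nausea and vomiting count as one item, the first row is 4 of 4 and the conclusion is the same. The label in {22} can be predicted in every case from the timing in {11b}, so timing is what it encodes.

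**Step 2: test the label against seriousness.** Section {22} gives no criterion by which hair loss is serious and hypoglycemia is not. The word seriousness appears only as one of four fields in the SAE report.

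**Step 3: test the prediction.** The argument is that the trial is short and therefore will have no SAEs. It follows only if an SAE is by definition a late event. The protocol itself does not fit this. Lipid profile change is on the SAE list, yet cholesterol, triglycerides, LDL and HDL are secondary outcomes assessed before and after the 8 weeks. Background and rationale {6a} reports lipid changes on the ketogenic diet, citing among its sources the reference that {11b} describes as a 6-week trial. Those changes were favourable, but {22} gives neither direction nor threshold for what it calls an SAE.

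**Step 4: follow the label to the reporting rule.** Of the 6 effects that the text places within a short time, 0 carry the label that has a stated DMEC route. The 5 that carry it are placed in long-term use.

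**Step 5: compare {30} with {11b} and {22}.** {30} reports no adverse effects for either diet. {11b} and {22} both list short-term adverse effects of the ketogenic diet. As worded, these statements cannot all stand.

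**The case against.** The strongest reply is that the lists are background and not a classification rule. They are introduced tentatively and as examples, and no sentence says that a trial event is to be graded by its date of onset or by its place on a list. The operative sentence asks for expectedness, seriousness, severity and causality, which are judged case by case. That stands in part: it suggests that individual assessment was intended. But the seriousness field is completed once an event has entered the SAE route, and the text does not reconcile the field with its own labels.

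Oversight is also more than nominal. Frequency and plans for auditing trial conduct {23} has the independent committee meeting every 2 weeks (8 / 2 = about 4 meetings during one woman's treatment) and following day-to-day progress, with weekly project management meetings. The dietitian calls every 2 weeks. These may well catch a serious early event. For that reason a reader who infers that such events will go unreported goes further than the documents allow.

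Sending only SAEs to a monitoring committee is ordinary practice and is no fault in itself. Nor is the absence of a full SAE definition, which an article may leave to the full protocol. The point here is narrower: what the article does state is a misclassification.

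On {30}, a reader might infer that it stretches a statement about serious complications of PLCD into a denial of any adverse effect for both diets. The documents do not support that, since {11b} also describes the cited short ketogenic-diet trials as free of adverse complications, and {30} may be a loose restatement of that. The conflict with the listed short-term effects remains.

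**Conclusion.** The point holds as a stated misclassification in the harms section that should be corrected. All 11 complications are labelled by timing, the prediction of no SAEs depends on that labelling, and the one stated reporting route to the DMEC uses the label. The consequence is a risk that a serious early event is handled as an AE, and that hair loss or an ordinary lipid change is counted as serious. It assumes that staff would read the lists as guidance on classification, which the text invites but does not order.

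The documents give no event frequencies, so no number of misdirected reports can be estimated, and nothing here affects the primary weight comparison. The wording of {30} is a minor inconsistency.

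**What to change.** In Adverse event reporting and harms {22}:

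- Call the two lists short-term and long-term complications of the ketogenic diet, and remove AE and SAE from them.
- Delete the sentence predicting no SAEs.
- State that any adverse event, in either arm and at any time, is an SAE if it causes death, threatens life, needs hospital admission or leaves lasting disability, and that every SAE is reported to the DMEC with the four fields already named.
- State that lipid changes are analysed as a secondary outcome and are SAEs only if they meet those criteria.
- Keep the existing instruction to stop the diet on any adverse effect.

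In Provisions for post-trial care {30}: limit the statement to the short trials cited in {11b}, and acknowledge the short-term effects listed for the ketogenic diet.

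The cost is wording in two sections. No visit, test or committee meeting is added. The downside is slightly more SAE reporting.

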### Frequency and plans for auditing trial conduct {23}

It is anticipated that every week, the project management group will meet to review trial conduct.

Also, the trial steering group as well as the independent data monitoring and ethics committee will meet to review conduct throughout the trial period, once every 2 weeks. In addition, the trial steering group (Iranian Steering Committee for Clinical Trials) as well as the independent data monitoring committee will observe the day-to-day progress of this trial. The ethics committee of the Kermanshah University of Medical Sciences will control the authenticity of the trial. The faculty of Nutritional Sciences and Food Technology is responsible for the scientific requirements.

### Plans for communicating important protocol amendments to relevant parties (e.g., trial participants, ethical committees) {25}

The researchers will conduct the study in compliance with the protocol provided. Any modifications to the protocol including study objectives, study design, eligibility criteria, sample sizes, or significant changes in the study that will impact study conduct, potential benefit, or safety of the study participant will be communicated with the ethical committee.

### Dissemination plans {31a}

In the end, the results of this work will be published as an article.

## Discussion

This trial is designed to determine whether PLCD or KD could have more beneficial effects for improving PCOS disease by measuring anthropometric indices, hormonal status, lipid profile, and quality of life questionnaire. According to the 2018 guidelines of the American Society for Reproductive Medicine (ASRM), the first line of treatment for PCOS is lifestyle adjustment, including diet control and exercise, with the weight control for women suffering from PCOS [33]. According to different studies, dietary interventions have been shown to eliminate clinical symptoms of PCOS, for instance, menstrual disorders, abnormal hormonal indicators, and ovulation [14, 34]. Thus, diet modification could play an important role in improving the clinical symptoms of PCOS. Although there has not been a univocal therapy for PCOS, several studies indicate the importance of macronutrient distribution especially carbohydrates in the diet of women with PCOS due to their effect on insulin secretion from the pancreas [35]. As the KD has the utmost 10% carbohydrate, it activates AMPK and SIRT-1, which have beneficial effects on glucose homeostasis and improving insulin sensitivity [36]. On the other hand, studies have shown that LCD regimens reduce the levels of glucose, IGF-1, IGFBP1, and insulin [17]. In addition, due to the importance of insulin receptors and compensatory hyperinsulinemia in the reduction of androgen excess in PCOS women, LCD could improve hyperandrogenism-related symptoms. Therefore, this novelty study is put forward to specify which diet, PLCD or KD, would have more advantageous effects on PCOS patients. As PCOS women display an atherogenic lipid profile (associated with elevated levels of low-density lipoprotein, triglycerides, and cholesterol, along with reduced levels of high-density lipoprotein), applying the Portfolio diet in combination with a low-carbohydrate diet will provide us with unique data about their effects on lipid profile in comparison with the KD [12]. In addition, this trial is a multi-disciplinary approach that has combined assessments of nutrition, psychology, lipid profile, and reproductive medicine. Hence, the result of the current study could give us a new and comprehensive insight into this multi-faced syndrome and give more information about prescribing therapeutic diets for PCOS patients. The current study will further provide evidence to inform and aid in the future dietary therapeutic management of women with PCOS. As lifestyle adjustment specifically diet has been shown to ameliorate the clinical symptoms of PCOS, there is no consensus on an optimal diet yet [37]. Thus, this trial will provide us with useful information about prescribing an efficient and effective diet with proper control of carbohydrate intake as an essential approach for PCOS women.

## Trial status

This trial was registered on irct.ir (IRCT20200912048693N3) on 2022 December 14. Thus, it is considered to start on 2023 May 20 and will end on 06 January 2023.

## Data Availability

No applicable.

## Abbreviations

BMI: Body mass index
DHEA: Dehydroepiandrosterone sulfate
FBM: Fat body mass
FBS: Fasting blood sugar
FSH: Follicle-stimulating hormone
HDL: High-density lipoprotein
HOMA_IR: Homeostasis model assessment-insulin resistance
KD: Ketogenic diet
LH: Luteinizing hormone
LBM: Lean body mass
LDL: Low-density lipoprotein
MM: Muscle mass
PCOS: Polycystic ovary syndrome
MUFAs: Monounsaturated fats
PLCD: Portfolio low-carbohydrate diet
RD: Registered dietitian
SHBG: Sex hormone-binding globulin
TBW: Total body water
TEE: Total energy expenditure
